**Methods:**

OTTILIA (Observational sTudy on antiThrombotic prevention in thrombophILIA and pregnancy loss) and FIRST (recurrent Failures in assIsted Reproductive Techniques) registries are two prospective, multicenter, observational studies to evaluate pregnancy or ART outcomes in consecutive women with previous reproductive failures after spontaneous or assisted conception, respectively. All enrolled women are observed from their first visit after positive pregnancy test (OTTILIA) or before commencing a new ART cycle (FIRST) until the end of pregnancy or ART procedure (negative pregnancy test/end of pregnancy, if successful cycle), respectively. Data are collected by means of questionnaires and recorded in a central database. Follow-up investigations are performed during hospital stay, routine clinical follow-up visits or telephone interviews. Primary outcome is live birth rate in the OTTILIA register and clinical pregnancy rate in the FIRST.

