### Participants

All consecutive women who meet the inclusion criteria for the OTTILIA or FIRST registries (Table 1) are recruited by participating Centers on admission after obtaining informed consent. Women eligible for the OTTILIA register can undergo thrombophilia test before conception, according to local policy. If the test is not available or the test was not prescribed by the physician, women included are considered as non- carriers. As far as FIRST, knowledge of thrombophilia status is not a prerogative of the register. However, when information is available, it will be considered in final analysis.

**Table 1 Tab1:** Inclusion and exclusion criteria of the OTTILIA and FIRST registries

OTTILIA	FIRST
Inclusion criteria	
• Pregnancy confirmed by urine/blood pregnancy test or ultrasound examination • Previous recurrent otherwise unexplained PL * ≥3 or 2 PL in the presence of at least 1 normal fetal karyotype* or • At least 1 previous IUFD * A loss after 20 weeks of a morphologically normal fetus*	• ART cycle at enrolment *First, second and third level ART cycles* • 2 or more implantation failures/losses of clinical pregnancies after ART (independently of the number of embryos transferred) *At least 2 previous cycles with negative pregnancy test and/or PL after a positive pregnancy test*
Exclusion criteria	
• Personal history of venous and/or arterial thromboembolism • Allergy to LMWHs • Uterine abnormalities • Cervical incompetence • Chromosomal abnormalities in parents • Known hemorrhagic diathesis	• Uterine abnormalities • Hydrosalpinx • Chromosomal abnormalities in parents • Known hemorrhagic diathesis • Previous inclusion in the study

*PL* pregnancy loss, *IUFD* intrauterine fetal death, *ART* assisted reproductive technologies, *LMWHs* low-molecular-weight heparins

Enrolled women are free to withdraw their informed consent and exit from the study.

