Baseline Clinical information: • Maternal age • Body Mass Index • Smoking habit • Reproductive history (previous spontaneous pregnancies, ART attempts) • Cause of infertility (female, male, mixed or idiophatic), • Personal and family history of VTE • Presence of inherited or acquired thrombophilias • Thrombophilic risk factors Index-ART cycle information: • Fertilization (autologous/heterologous) • Type of ART procedure (IUI, IVF, ICSI, Other) • Ovarian stimulation (brand, doses/day, duration) • Antithrombotic prophylaxis (brand, doses/day, duration), • Number of oocytes retrieved •Number of embryo transfers	Follow-up ART outcomes: • Clinical pregnancy • Live birth (gestational age, delivery mode, sex, birth weight, fetal or maternal hemorrhage) • Obstetric complications (PL, IUFD, gestational hypertension, preeclampsia, HELLP syndrome, SGA newborns, placental abruption) • OHSS (time of occurrence after ovarian stimulation, severity, estradiol levels pg/ml, treatment) • VTE

*VTE* venous thromboembolism, *IUI* intrauterine insemination, *IVF* in vitro fertilization, *ICSI* intracytoplasmic sperm injection, *PL* pregnancy loss, *IUFD* intrauterine fetal death, *SGA* small-for-gestational age, *OHSS ovarian hyperstimulation syndrome*

The primary outcome is the live birth rate in the OTTILIA register and live birth or clinical pregnancy rate in the FIRST. The definition of all primary and secondary outcomes is provided in Table 3.

**Table 3 Tab3:** Definitions of primary and secondary outcomes in the OTTILIA and FIRST registries

	Definitions	Source
Clinical pregnancy	A pregnancy confirmed by ultrasonographic visualization of gestational sac or fetal heartbeat	Wang X et al. Fertil Steril 2003; 79: 577–9.
Live birth	The delivery of a live newborn	https://www.gfmer.ch/Medical_education_En/Live_birth_definition.htm
Pregnancy loss (PL)	A loss occurring ≤20 weeks	Regan L. BMJ 1991; 302: 543–4
Intrauterine fetal death (IUFD)	A loss occurring after 20 weeks	Royal College of Obstetricians & Gynaecologists. Late intrauterine fetal death and stillbrith (Green-top Guideline 55). London: Royal College of Obstetricians & Gynaecologists; 2010 [cited 2019 May 30]
Preterm birth	The delivery of an infant before completion of 37 weeks gestation	ACOG Committee Opinion No 579: definition of term pregnancy. Obstet Gynecol. 2013;122: 1139–40

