### Study size estimation

In the literature, the likelihood of observing live births without any treatment is estimated to range between 55 and 80% [2]; a multicentre Italian study [9] showed the occurrence of complications in 50% of all untreated women during pregnancy. Given these estimates, for the OTTILIA register, in order to observe an absolute increase of 15–20% (statistical power: 80%, significance level: 0.05), we calculated the inclusion of 190–340 thrombophilic women and, simultaneously, a cohort of pregnant women with the same clinical history (see inclusion criteria) not carrying inherited thrombophilia, in a ratio of at least 1:1. Thus, an overall number of 380–680 consecutive pregnancies are needed.

As far as the FIRST register is concerned, we estimated the inclusion of 624 women. This estimate is calculated on the basis of (1) the probability of observing live births after ART procedures (20–30%), (2) the estimate of an absolute increase of 5–10% in the number of live births after a prophylaxis of LMWHs (statistical power: 80%, significance level: 0.05).

It has been estimated that the OTTILIA and FIRST registries will be executed in the periods February 2012–December 2020 and October 2015–September 2020, respectively. In both the registries, an additional period of 9 months from the date of the last enrollment will be considered.

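### In FIRST, clinical pregnancy as primary outcome counts a repeated loss of a clinical pregnancy as a success and cannot register an LMWH effect confined to later losses

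*Protocol article*

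**What the plan says.** **Entry.** Table 1 (Participants) admits to FIRST women with "2 or more implantation failures/losses of clinical pregnancies after ART", and explains this as "At least 2 previous cycles with negative pregnancy test and/or PL after a positive pregnancy test". The population is therefore mixed: repeated implantation failure, repeated loss, or both.

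**Primary outcome.** The Abstract (Methods) states: "Primary outcome is live birth rate in the OTTILIA register and clinical pregnancy rate in the FIRST". The Study procedure section instead gives "live birth or clinical pregnancy rate in the FIRST".

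**Definitions.** Table 3 defines clinical pregnancy as "A pregnancy confirmed by ultrasonographic visualization of gestational sac or fetal heartbeat". It does not require the pregnancy to continue. Pregnancy loss (PL) is "A loss occurring ≤20 weeks", so it can follow a clinical pregnancy.

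**Sample size.** The Study size estimation section sizes FIRST at 624 women from a live birth probability of 20–30% and "an absolute increase of 5–10% in the number of live births after a prophylaxis of LMWHs", with 80% power and a 0.05 significance level.

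**Data.** Table 2 lists clinical pregnancy, live birth, PL and intrauterine fetal death (IUFD) as FIRST follow-up items, and observation continues to the end of any pregnancy.

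**The concern.** For women who came in through loss of a clinical pregnancy, the event that made them eligible and the event scored as success overlap. A sac followed by another miscarriage is the same failure again, yet it enters the primary analysis as a favourable result.

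Two errors could follow in the primary result. A treatment that prevents later losses would show nothing on it. A factor that only produces more pregnancies which are then lost would look beneficial on it.

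This is not only a matter of inconsistent wording. Writing clinical pregnancy everywhere would remove the contradiction between sections and leave this problem in place.

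**Working it through.** **1. Which outcomes count as success.** Take a woman with two earlier losses of clinical pregnancies and follow the index cycle through the Table 3 definitions:

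| Index cycle | Clinical pregnancy | Live birth |
|---|---|---|
| Negative test | failure | failure |
| Positive test, lost before ultrasound | failure | failure |
| Sac or heartbeat, then PL or IUFD | **success** | failure |
| Sac or heartbeat, then live birth | success | success |

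The two outcomes differ only in the third row, which is her qualifying failure.

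**2. The Study procedure wording read as a composite.** Every live birth has first been a clinical pregnancy. The set of women with either event is therefore the set with a clinical pregnancy, and the composite rate equals the clinical pregnancy rate.

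**3. Reproducing the 624.** Inputs from the Study size estimation section: live birth 20% against 30%, power 80%, significance level 0.05. Assumed: two-sided test, 1:1 split, no dropout.

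- Pooled term: √(2 × 0.25 × 0.75) = 0.6124. Unpooled term: √(0.20 × 0.80 + 0.30 × 0.70) = 0.6083.
- n per group = (1.960 × 0.6124 + 0.8416 × 0.6083)² / 0.10² = 293.2, rounded up to 294, or 588 in total.
- With continuity correction: (293.2 / 4) × [1 + √(1 + 4 / (293.2 × 0.10))]² = 312.8, rounded up to 313, or 626 in total.

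The stated 624 is within 2 women of this. It is a live birth calculation for the pair 20% and 30%.

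**4. Power on live birth with 312 per group.** z = (0.10 × √312 − 1.960 × 0.6124) / 0.6083 = (1.766 − 1.200) / 0.6083 = 0.93, so power is 82%.

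**5. Power on clinical pregnancy if the effect falls wholly after ultrasound confirmation.** The clinical pregnancy rates in the two groups are equal and the true difference is 0. The test rejects at its significance level, 5%, at any sample size. This needs no assumed pregnancy rate.

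**6. What a 20% to 30% rise in live birth would then mean.** Loss per clinical pregnancy = 1 − live birth / clinical pregnancy. The clinical pregnancy rate in FIRST is not given, so a range is shown. The 33.8% is the general IVF pregnancy rate per transfer in the Background, not a figure for this population.

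| Assumed clinical pregnancy, both groups | Loss at 20% live birth | Loss at 30% live birth |
|---|---|---|
| 30% | 33% | 0% |
| 33.8% | 41% | 11% |
| 35% | 43% | 14% |
| 40% | 50% | 25% |

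**7. A mixed population (illustration only).** Assume 35% clinical pregnancy and 20% live birth in untreated women of both entry types. Women who entered by loss respond only after implantation. The others respond at implantation, from 35% to 52.5%; with loss unchanged at 43%, their live birth is 0.525 × (0.20 / 0.35) = 30%. Live birth then rises from 20% to 30% in everyone, with 82% power.

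- Half entered by loss: clinical pregnancy difference 0.50 × 17.5 = 8.8 points (35% against 43.8%), power 61%.
- Three quarters entered by loss: 0.25 × 17.5 = 4.4 points (35% against 39.4%), power 20%.

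**The case against.** **The registry is not blind to losses.** A reader might infer that FIRST could not see an LMWH effect on losses at all, or would be bound to report no benefit. The document does not support that. Live birth, PL and IUFD are collected to the end of pregnancy, and the Statistical analysis plan section tests associations with drugs and regimens for secondary as well as primary outcomes. The blindness belongs to the clinical pregnancy outcome only. This part of the objection stands.

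**Live birth may already be primary.** "live birth or clinical pregnancy rate in the FIRST" can be read as two alternative primary outcomes, since Tables 2 and 3 keep them apart. That reading is possible, but it leaves the choice open and conflicts with the Abstract, so it does not settle the matter.

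**Loss is only one entry route.** For women with repeated implantation failure, clinical pregnancy measures their qualifying failure. A loss after a positive test but before ultrasound also qualifies, and its repeat is not scored as success. Both limits stand, and the share of women affected is not given.

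**The mechanism is hypothetical.** The Background presumes obstruction of placental vessels but also cites LMWH for outcomes of ART procedures generally. It does not confine the action to established pregnancy, so a purely late effect is a scenario, not a prediction. Moreover, 82% applies to the favourable end of the planned range: for a 5-point rise from 20%, live birth itself has only about 32% power with 312 per group.

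**Conclusion.** The point holds for the primary outcome as the Abstract states it, and equally if the Study procedure wording is read as a composite. Two parts rest on definitions alone: a repeat loss after ultrasound confirmation counts as success, and an effect confined to such losses leaves the primary outcome unchanged, with rejection at 5%.

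The contrast with 82% for live birth assumes 20% against 30%, a two-sided test and 312 women per group. The 1:1 split is an assumption, because LMWH use in FIRST follows local practice. The intermediate figures of 61% and 20% also depend on an assumed 35% clinical pregnancy rate, assumed shares by entry route and an assumed split of the mechanism. They show direction rather than expected size.

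The change is worth making: the main result would otherwise rest on an outcome that ignores one of the failures for which FIRST enrols, while the sample size already rests on live birth.

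**What to change.** Name live birth per woman as the single FIRST primary outcome, in both the Abstract and the Study procedure section, in line with the Study size estimation section. Make clinical pregnancy a secondary outcome.

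The 624 does not change, because it is already a live birth calculation. Data collection does not change either, because live birth is recorded and women are followed to the end of pregnancy. The cost is that the primary result comes some months later than a clinical pregnancy analysis would.

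Optionally, report results by type of qualifying failure: negative tests only, against at least one PL after a positive test. This depends on what the recorded history allows. Table 2 lists ART attempts without saying whether losses before and after ultrasound confirmation are distinguished, so a finer split may not be recoverable.

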### Study procedure

All enrolled women are observed from their first visit after positive pregnancy test (OTTILIA) or before commencing a new ART cycle (FIRST) until the end of pregnancy or ART procedure (negative pregnancy test/end of pregnancy, if successful cycle), respectively.

At baseline, clinical information and index- pregnancy/ART cycle details are obtained from all women by a specially trained staff (Table 2). Data are collected by means of questionnaires and recorded in a web-based database including an electronic form for each woman enrolled. To ensure high quality data, a centralized data management performs quality control and plausibility checks according to predefined procedures. Follow-up data (Table 2) are collected during the three trimesters of pregnancy and in the puerperium period (6 weeks after delivery), at the time of hospital stay, routine clinical follow-up visits or telephone interviews.

**Table 2 Tab2:** Baseline and Follow-up data for evaluation and monitoring of women enrolled in the OTTILIA and FIRST registries

OTTILIA	
Baseline Clinical information: • Maternal age • Body Mass Index • Smoking habit • Reproductive history (previous pregnancies and obstetric complications occurred) • Personal and family history of VTE • Presence of inherited or acquired thrombophilias • Thrombophilic risk factors Index-pregnancy information: • Results of performed imaging tests, (ultrasonography, Doppler ultrasonography) • Invasive prenatal testing (i.e. villous sampling, amniocentesis) • Antithrombotic prophylaxis (brand, doses/day, duration)	Follow-up Pregnancy outcomes: • Live birth (gestational age, delivery mode, sex, birth weight, fetal or maternal hemorrhage) • Obstetric complications (PL, IUFD, gestational hypertension, preeclampsia, HELLP syndrome, SGA newborns, placental abruption) • VTE
FIRST	
Baseline Clinical information: • Maternal age • Body Mass Index • Smoking habit • Reproductive history (previous spontaneous pregnancies, ART attempts) • Cause of infertility (female, male, mixed or idiophatic), • Personal and family history of VTE • Presence of inherited or acquired thrombophilias • Thrombophilic risk factors Index-ART cycle information: • Fertilization (autologous/heterologous) • Type of ART procedure (IUI, IVF, ICSI, Other) • Ovarian stimulation (brand, doses/day, duration) • Antithrombotic prophylaxis (brand, doses/day, duration), • Number of oocytes retrieved •Number of embryo transfers	Follow-up ART outcomes: • Clinical pregnancy • Live birth (gestational age, delivery mode, sex, birth weight, fetal or maternal hemorrhage) • Obstetric complications (PL, IUFD, gestational hypertension, preeclampsia, HELLP syndrome, SGA newborns, placental abruption) • OHSS (time of occurrence after ovarian stimulation, severity, estradiol levels pg/ml, treatment) • VTE

*VTE* venous thromboembolism, *IUI* intrauterine insemination, *IVF* in vitro fertilization, *ICSI* intracytoplasmic sperm injection, *PL* pregnancy loss, *IUFD* intrauterine fetal death, *SGA* small-for-gestational age, *OHSS ovarian hyperstimulation syndrome*

The primary outcome is the live birth rate in the OTTILIA register and live birth or clinical pregnancy rate in the FIRST. The definition of all primary and secondary outcomes is provided in Table 3.

**Table 3 Tab3:** Definitions of primary and secondary outcomes in the OTTILIA and FIRST registries

	Definitions	Source
Clinical pregnancy	A pregnancy confirmed by ultrasonographic visualization of gestational sac or fetal heartbeat	Wang X et al. Fertil Steril 2003; 79: 577–9.
Live birth	The delivery of a live newborn	https://www.gfmer.ch/Medical_education_En/Live_birth_definition.htm
Pregnancy loss (PL)	A loss occurring ≤20 weeks	Regan L. BMJ 1991; 302: 543–4
Intrauterine fetal death (IUFD)	A loss occurring after 20 weeks	Royal College of Obstetricians & Gynaecologists. Late intrauterine fetal death and stillbrith (Green-top Guideline 55). London: Royal College of Obstetricians & Gynaecologists; 2010 [cited 2019 May 30]
Preterm birth	The delivery of an infant before completion of 37 weeks gestation	ACOG Committee Opinion No 579: definition of term pregnancy. Obstet Gynecol. 2013;122: 1139–40
Gestational hypertension (GH)	Blood pressure ≥ 140/90 mmHg after 20 weeks of gestation in a previously normotensive woman	www.nice.org.uk/guidance/cg107
Preeclampsia	Blood pressure ≥ 140/90 mmHg and proteinuria of 0.3 g or more in a 24-h urine specimen occurring after 20 weeks of gestation in a previous normotensive woman	www.nice.org.uk/guidance/cg107
HELLP syndrome	Thrombocytopenia (i.e. platelet count < 150,000 cells/μL), elevated AST and/or ALT (> 40 IU/L), increased LDH (> 600 IU/L), and hemolysis (increased LDH level)	Martin JN et al. Am J Obstet Gynecol 1999; 180: 1373–84.
Small-for-gestational age (SGA) newborns	Apparently healthy neonate with birthweight <10th centile for gestational age in the absence of infection and maternal drug or alcohol abuse	RCOG. The investigation and management of the small–for–gestational–age fetus. Green-top Guideline. 2nd ed.; 2014
Placental abruption	The early separation of the placenta from the uterus	Ananth CV, et al. Am J Obstet Gynecol. 2016;214: 272
Ovarian hyperstimulation syndrome (OHSS)	An exaggerated systemic response to ovarian stimulation with a wide spectrum of clinical and laboratory manifestation. According to the degree of manifestations it is classified as mild, moderate, or severe.	Humaidan P, et al. Hum Reprod. 2016;31: 1997–2004
Venous thromboembolism (VTE)	Deep vein thrombosis (DVT), defined as a blood clot in deep veins of the legs with or without pulmonary embolism (PE). DVT is diagnosed if confirmed by Doppler ultrasound exam. PE diagnosis is confirmed by ventilation-perfusion lung scanning, angiography, or computed tomography. Pregnancy-related VTE is defined as a VTE occurring during the pregnancy or in the puerperium (within 6 weeks after delivery).	Kearon C, et al., Chest 2012; 141 (2 Suppl): e419S-e496S.
Hemorrhage.	Bleeding events. They are classified as major or minor according the ISTH criteria. Wound hematoma in case of caesarean section	Schulman S, J Thromb Haemost 2005; 3: 692–4.

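### FIRST's primary outcome differs between the Abstract and the Methods, and its 624 women are sized on live birth alone

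*Protocol article*

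**What the plan says.** Three places in the protocol article bear on FIRST's primary outcome.

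- **Abstract, Methods:** "Primary outcome is live birth rate in the OTTILIA register and clinical pregnancy rate in the FIRST".
- **Study procedure, before Table 3:** "The primary outcome is the live birth rate in the OTTILIA register and live birth or clinical pregnancy rate in the FIRST".
- **Study size estimation:** "As far as the FIRST register is concerned, we estimated the inclusion of 624 women". The inputs are a live-birth probability of 20–30% after ART and "the estimate of an absolute increase of 5–10% in the number of live births after a prophylaxis of LMWHs", with "statistical power: 80%, significance level: 0.05".

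Table 3 defines the two outcomes separately. Clinical pregnancy is "A pregnancy confirmed by ultrasonographic visualization of gestational sac or fetal heartbeat" and live birth is "The delivery of a live newborn". It defines no composite of the two. The statistical analysis plan section of the article applies one threshold, p below 0.05, and gives no order of testing, co-primary rule or split of the significance level. For OTTILIA the primary outcome is live birth in both the Abstract and the Methods, so the inconsistency is confined to FIRST.

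**The concern.** Clinical pregnancy and live birth answer different questions. A treatment could change implantation without changing the number of live births, or reduce later losses without changing the clinical pregnancy rate. A report from FIRST could therefore differ according to which outcome is treated as primary.

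An article may leave much to a full protocol or analysis plan, but here it does state the primary outcome and states it in ways that do not match. Treatment with LMWH is not randomised, and its possible benefit is part of a primary aim. A single outcome fixed in advance is one of the few safeguards such a registry has against selective emphasis. The power statement is also tied to an outcome that the Abstract does not name as primary.

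**Working it through.** **1. Reproduce the 624.** Inputs from Study size estimation: live birth 20% rising to 30%, power 80%, significance level 0.05. Assumed, because not stated: two-sided test, equal groups, no allowance for dropout.

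n per group = [1.960·√(2·p̄(1−p̄)) + 0.842·√(p1(1−p1) + p2(1−p2))]² / (p2−p1)²

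With p1 = 0.20, p2 = 0.30 and p̄ = 0.25: (1.200 + 0.512)² / 0.01 = 293.2, so 294 per group and 588 in total.

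Continuity correction: n/4 · [1 + √(1 + 4/(n·|p2−p1|))]² = 312.8, so 313 per group and **626 in total**. Rounding 312.8 down instead gives 2 × 312 = 624.

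Over baselines of 20, 25 and 30% and gains of 5, 7.5 and 10 points, with equal groups, only this combination comes within 2 women of 624. The stated size is a live-birth calculation.

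**2. Try each reading of the Methods wording.**

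| Reading | Agrees with Abstract? | Agrees with sample size? |
|---|---|---|
| Composite: either event counts | Yes, in substance, because a live birth follows a clinical pregnancy | No: sized on live birth |
| Two alternatives, either may be primary | No: Abstract names one | Only for the live-birth half |
| Live birth alone | No | Yes |

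No row has yes in both columns.

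**3. Type I error if both are tested at 0.05 and either can count.** Live births are nested in clinical pregnancies. With live-birth rate p_L and clinical pregnancy rate p_C, the correlation is

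φ = √[p_L(1−p_C) / (p_C(1−p_L))]

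and the error is P(|Z1| > 1.96 or |Z2| > 1.96) for a bivariate normal with correlation φ. The live-birth range is the article's. The clinical pregnancy range of 30–40% is an assumption.

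| p_L | p_C | φ | Error |
|---|---|---|---|
| 20% | 30% | 0.76 | 8.0% |
| 20% | 40% | 0.61 | 8.7% |
| 25% | 30% | 0.88 | 7.2% |
| 25% | 35% | 0.79 | 7.9% |
| 25% | 40% | 0.71 | 8.3% |
| 30% | 35% | 0.89 | 7.1% |
| 30% | 40% | 0.80 | 7.8% |
| 30% | 30% | 1.00 | 5.0% |

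The last row is the limiting case in which every clinical pregnancy ends in a live birth. Simulation with 312 women per group gave 7.2–8.4% over six assumed pairs of rates. Two independent tests would give 1 − 0.95² = 9.75%, which is the ceiling.

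**4. Power if clinical pregnancy is primary.** The article gives no planning rate or effect for it. As an illustration I take the pregnancy rates per transfer from the Background (32.3% for ICSI, 33.8% for IVF), an assumed 10-point gain and 312 per group:

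power = Φ{[|p2−p1|·√n − 1.960·√(2p̄(1−p̄))] / √(p1(1−p1) + p2(1−p2))}

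- 32.3% to 42.3%: (1.766 − 1.340) / 0.680 = 0.626, power 73.4%; 80% power needs 732 women.
- 33.8% to 43.8%: (1.766 − 1.351) / 0.686 = 0.606, power 72.8%; 80% power needs 744 women.
- 23.1% to 33.1% (frozen embryo replacement): power 79.5%; 80% power needs 632 women.

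These figures carry no continuity correction. On the same basis live birth 20% to 30% has 82.4%. With the correction the comparison is about 80% for live birth against 70–71% at the ICSI and IVF rates.

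**The case against.** Several points on the other side stand.

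- **Only two places state a primary outcome.** The sample size section gives a planning outcome and does not call it primary. A reader might infer three rival primary outcomes. The text supports two differing statements and a calculation built on live birth.
- **The composite reading is possible.** It would bring the Abstract and Methods into line in substance, leaving only the mismatch with the sample size. The alternatives reading, on which the type I figures depend, is permitted by the wording but not stated.
- **Selection after the fact is not shown.** A reader might infer that the headline result will be picked once the data are in. The text fails to rule that out, but nothing in it shows such an intention. FIRST has a registration number, and its registry record, which may name one outcome, is not at hand.
- **The detectable difference is no argument here.** A reader might set the roughly 10.7–10.9 points detectable at a 30–33% baseline against the planned 5–10 and blame clinical pregnancy. But live birth at 30%, the top of the planning range, has the same 10.7 points, and at 20% it has 9.7. That 5 points is out of reach is a separate matter, common to both outcomes.
- **FIRST is an observational registry with broad aims and many tests of association.** Naming one outcome will not hold the error at 5% across all of them, and confounding is likely a larger threat than a few points of type I error.
- **Clinical pregnancy is a plausible outcome** for women enrolled after implantation failures, so live birth is not the only defensible choice.

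None of this makes the three places agree.

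**Conclusion.** The point holds as an internal contradiction: the Abstract, the Methods and the sample size cannot all be right about FIRST's main outcome. That conclusion rests on the text alone.

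The sizes rest on assumptions. The type I error of about 7–9%, falling to 5% when the rates coincide, needs the alternatives reading and an assumed clinical pregnancy rate of 30–40%. The power of about 73% needs an assumed 10-point gain, equal groups and a 32–34% baseline borrowed from general ART figures, not from women with repeated failures. Part of that shortfall comes from the higher baseline itself: live birth at 30% has 74.6% by the same formula. It would go too far to say that error rate and power are undefined. Power is defined for live birth, and what is missing is agreement that live birth is the primary outcome.

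**What to change.** Name one primary outcome for FIRST and state it identically in the Abstract, in Study procedure and in Study size estimation. List the other as secondary. Record the date of and reason for the choice, because the stated study period runs from October 2015 and changing what one section calls primary is more than an edit of wording.

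- **If live birth is chosen,** the 624 stands as the basis already given, and the outcome is already in the follow-up data (Table 2). The cost is that the main result waits for delivery.
- **If clinical pregnancy is chosen,** state a planning rate and effect for it and recalculate the sample size or power. At the illustrative rates in the working, 80% power for a 10-point gain needs 732–744 women without continuity correction.
- **If both are meant to be primary,** say so and give the rule for combining or ordering the two tests, with the sample size to match.

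None of these options needs new data items.
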